# 8. STATISTICAL ANALYSIS

Data will be analysed by the intention-to-treat principle. Demographic characteristics, variables from laboratory analysis and quantitative variables obtained from the clinical evaluation (Pain score, opioids consumption) will be reported as means, medians or percentages together with their standard deviations, as appropriate.

We will perform the following analysis of the primary endpoint. In all patients we test for a difference in mean pre- and post-operative extension angles between those with and without Cryoseal. Adjusting for pre-operative extension angles by analysis of covariance, we perform a two-sided test at level 0.049. In a secondary analysis, Fisher’s exact test will be used to determine the effect of use of fibrin sealant on adverse events. We will investigate whether the Cryoseal effect is modified by the use of a drain by adding drain use and the interaction between drain use and Cryoseal to the above analysis of covariance model. Also, effects within various other patients groups will be studied (e.g. gender, age, adipositas and rheumatic disorders)

Interim analysis and stopping rule:

We plan to perform a single interim analysis when a total of 250 patients have been included. At this time we will decide if the trial should be terminated early for efficacy. In all patients we test for a difference in mean pre- and post-operative extension angles between those with and without Cryoseal. Adjusting for pre-operative extension angles, we perform a two-sided test at level 0.005. If we are able to reject the null hypothesis, we terminate the trial and conclude efficacy of the treatment.

If the stopping rule is not met and the trial continues, we must set the level of significance of the final analysis to 0.049 to account for the fact that we performed an interim analysis. This is referred to as the O'Brien-Fleming rule.

Also, if the trial continues, we will use the available data to estimate the standard deviation of the primary outcome. Based on this estimate, we will re-compute the sample size that is needed to achieve 90% power to detect a 10 degree difference between the study arms at level 5%. We will adjust the sample size accordingly. However, we will not include less than 400 patients or more than 600 patients.

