**Analysis plan**

The study database will be closed and subsequently be de-blinded more than six weeks after the last surgery procedure of the FIRST-patients. This analysis plan will be registered at the Dutch trial register (NTR) and the ethics committee will be informed about protocol 4.1 before execution of the plan using the data from the closed database. The primary analysis will be performed as stated in the protocol. Subsequently, a for three variables stratified subgroup analyses of the primary end points will be performed. This will be folllowed by a pre-specified subgroup analyses using 19 variables for hypothesis screening.

Statistical analyses

In SPSS, for each subgroup the odds ratio (OR under randomized controlled conditions) or relative risk (by univariate- and multivariate analysis (MVA)) with the corresponding 95% confidence interval (CI) will be estimated for CryoSeal. Although subgroups of the study population are predominately formed based on confounding factors, we will investigate the stability of the effect estimates over different levels of the confounding factors by correction in the MVA for those confounders. When a preoperative variable is significantly associated with CrySeal use we will address this observation, however we continue the primary and secondary analysis using the pre-specified subgroups.

Confounding and effect modification

Normally the problem of confounding by indication is virtually absent in the study of side effects of medical interventions. In case of CryoSeal use however, the subgroup analyses does not correct for the possibility of effect modification. Effect modification could arise since patients when for example wound drains were placed and could change the susceptibility of the patients for effects by CryoSeal.

Interpretation of pre-specified subgroup analyses and “multiple testing”

The stratified subgroup analyses will be made with each pre-specified subgroups. There will be no correction for multiple testing because all subgroups are defined by variables which are known to have underlying associations with the primary endpoints of the study. All subgroups were specified before the data are available. The implications of the outcomes will be discussed in relation to all other associated estimates observe in all subgroups.

The Plan of pre-specified subgroup analyses

Subgroup analyses:

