After subsequent primary and secondary analysis of the effect of CryoSeal using the primary and secondary endpoints as presented in Protocol 4.1 of the total RCT dataset, according to intention to treat (ITT) and according to treatment (ATT), also pre-specified subgroup analyses of the putative effects on the primary and secondary endpoints (estimated odds ratio (OR) and 95% interval between both study-arms) of CryoSeal will be performed.

1. The following hypotheses will be tested using three for the variables stratified subgroups:

1. Catheter use and no catheter use
2. NSAID-users and no NSAID-users
3. Age > 70 and ≤ 70 years, or categorized in 3 equal sized samples of age (for example: <60, 60-70, >70)

The corresponding hypotheses are:

1. Catheter can disturb the CS-sealing process of the wound and therefore decrease the postoperative knee ROM and mobility effect of CS

2. NSAID-use are prescribed to reduce pain perception and as anti-coagulation medication, which decrease postoperative knee ROM and mobility effect of CS

3. Age is associated with increased co-morbidity resulting in reduced wound healing, which increase postoperative knee ROM and mobility effect of CS in patients > 60 years

2. Separated in the CryoSeal arm and in the non-CryoSeal patients the following 19 pre-specified subgroups will be selected for MVA to identify whether these factors are important or not in the CS-effect. Subsequently, using the total study cohort de following subgroups are analysed by dichotomic (or continuous) comparison (Y/N) between CryoSeal use or not:

Combined subgroups using 4 variables:

1. Catheter use and no catheter use
2. NSAID-users and no NSAID-users
3. Age > 70 and ≤ 70 years, or categorized in 3 equal sized samples of age (for example: <60, 60-70, >70)
4. Women and men

Single subgroups using each variable (or not):

1. Peroperative Hb ≤ 6 mmol/L and > 6 mmol/L
2. Transfused and non transfused patients
3. Prednison-users and no Prednison users
4. Cemented and no cemented protheses
5. “Bloedleegte” surgery and no “bloedleegte” surgery
6. If catheter use: Bellovac and no low-vac catheter use
7. If transfused: trigger of perioperative RBC use at Hb ≤ 6 mmol/L and > 6 mmol/L
8. If transfused: Age> 60 and age ≤ 60 with trigger of perioperative RBC use at Hb ≤ 6 mmol/L
9. Surgery time > 2 hr and < 2 hr

Stepwize variables:

1. When drain used: Wound salvage production or not (Y/N)
2. When salvage production, reinfusion or not

Continuous variable:

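### Correcting for a factor in the multivariate model gives one averaged CryoSeal effect, so it cannot show whether the effect is stable over that factor's levels; a between-level contrast is planned for drain use only

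*Combined protocol and SAP*

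**What the plan says.** The addendum (Analysis plan, Statistical analyses) treats the subgroup factors largely as confounders and says "we will investigate the stability of the effect estimates over different levels of the confounding factors by correction in the MVA for those confounders". It names no interaction term, heterogeneity test or threshold. Its paragraph on confounding and effect modification concedes that "the subgroup analyses does not correct for the possibility of effect modification".

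The effect measure per subgroup is an odds ratio or a relative risk with 95% CI. The subgroup section repeats this for the primary and secondary endpoints as "estimated odds ratio (OR) and 95% interval between both study-arms".

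That section then poses three hypotheses, each that a factor changes the size of the CryoSeal effect: catheter use, NSAID use and age. For the longer list it says "Separated in the CryoSeal arm and in the non-CryoSeal patients the following 19 pre-specified subgroups will be selected for MVA", followed by comparisons by CryoSeal use in the whole cohort.

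The section on extra observational analyses pools over strata when, among other conditions, the estimates are homogeneous. It does not say how homogeneity is judged.

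Protocol Section 8 contains one formal contrast between levels, for the primary endpoint: "adding drain use and the interaction between drain use and Cryoseal to the above analysis of covariance model".

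**The concern.** Whether an effect is stable over levels is a question about the difference between the level-specific effects. Adjusting for the factor answers a different question: what the average effect is with the factor held constant. CryoSeal is randomised, so a factor fixed before surgery confounds it only by chance, and adjusting for such a factor mainly gains precision.

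Two things are at stake. First, the hypotheses on NSAID use and age have no stated analysis that compares the effect between levels. Second, the pooling rule needs a judgement of homogeneity, and the only method the addendum names for stability cannot supply one.

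There is a lesser problem with the odds ratio. It is non-collapsible: adding a prognostic factor to the model can move it although the effect is constant and the arms are perfectly balanced. Such a movement should not be read as confounding or instability.

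**Working it through.** **Inputs from the protocol (Section 4.4):** difference 10 degrees, SD 35 degrees, 250 patients per arm, two-sided level 4.9%, stated power 90%. **Assumptions:** a factor split 50:50 and unrelated to arm, N = 500, and all event risks and factor strengths. The documents give none of these risks.

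**1. The plan's own figure.** SE = 35 × √(2/250) = 3.130 and 10/3.130 = 3.194. The critical value at 4.9% is 1.969, so power = Φ(3.194 − 1.969) = Φ(1.225) ≈ 0.89, against 90% stated. It reproduces to about one point. The present point does not rest on it.

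**2. A varying effect in degrees.** Effects are 20 at one level and 0 at the other.
- Crude effect: (20 + 0)/2 = 10.
- Main-effects correction with balanced levels weights them equally, again giving 10. Simulation at N = 500 gave a mean corrected effect of 9.96 and a mean change on correction of 0.00 (SD 0.69).
- The quantity asked for is 20 − 0 = 20 degrees, and correction does not show it.

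**3. A varying odds ratio.**
- Level odds ratios 3 and 1/3, control risk 50% at both levels: treated risks are 75% and 25%, mean 50%, so the crude OR is 1.00. The corrected OR is also 1.00. The interaction is ln 9 = 2.197. With 125 patients per cell its variance is 2 × [1/(125 × 0.25) + 1/(125 × 0.1875)] = 2 × (0.0320 + 0.0427) = 0.149, SE 0.386, z ≈ 5.7.
- Level odds ratios 4 and 1, control risk 30%: crude 2.03, corrected 2.08, interaction z ≈ 3.6.
- Level odds ratios 4 and 1, control risks 20% and 60%: crude 1.83, corrected 1.91. Here correction moves the figure slightly, but still does not reveal the variation.

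**4. A constant odds ratio of 2, no confounding.** Worked case: central control risk 30%, factor OR 3. Control risks by level are 19.8% and 42.6% (mean 31.2%); treated risks are 33.1% and 59.8% (mean 46.4%). The crude OR is 0.867/0.454 = 1.91 and the corrected OR is 2.00, a shift of 4.8%. Over a range:

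| Central control risk | Factor OR 2 | 3 | 5 | 10 |
|---|---|---|---|---|
| 5% | 0.5% | 1.3% | 2.7% | 5.3% |
| 10% | 1.0% | 2.4% | 4.9% | 9.6% |
| 30% | 1.9% | 4.8% | 9.9% | 19.2% |
| 50% | 2.0% | 4.9% | 10.2% | 19.8% |

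For comparison, the 95% CI for an OR of 2 at N = 500 is about 1.40 to 2.85. The shift is zero when CryoSeal has no effect. A constant relative risk of 1.5 stays 1.5, and a mean difference does not drift in this way.

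**5. What a between-level contrast can detect.** In degrees, SE = 35 × √(4/125) = 6.26. At two-sided 5%, a 20-degree difference between levels has power Φ(20/6.26 − 1.96) ≈ 89%, and a 10-degree difference Φ(10/6.26 − 1.96) ≈ 36%.

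**The case against.** The strongest reply is that a varying effect is not hidden. The addendum already estimates the effect with a 95% CI in each subgroup, so an effect present at one level and absent at the other would appear in the tables. That stands: what is missing is the contrast between the estimates, not the estimates. A reader might infer that the plan as a whole would report unstable effects as stable. The documents do not support this.

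Nor do they support the inference that stability will be decided by comparing crude with corrected figures. No such rule or threshold is written, and the sentence might mean level-specific estimates adjusted for the other factors. The wording leaves this open. On the plain reading, correction is the named tool, and it still gives an average.

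Drain use does have an interaction term in Section 8. Catheter in the addendum appears to mean the wound drain, so one of the three hypotheses is covered for the primary endpoint. NSAID use and age are not.

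A reader might also object strongly to the line "When a preoperative variable is significantly associated with CrySeal use we will address this observation". Testing preoperative variables against a randomised arm picks up only chance. But the same sentence goes on to say that the planned analyses continue regardless, and the documents give no count of preoperative variables from which to calculate a false-alarm rate. Most of the listed factors arise during or after surgery. Little rests on this.

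Finally, these analyses are labelled exploratory. That limits the consequences but does not make the named method suitable.

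**Conclusion.** The point holds in a narrow form. The addendum sets out to examine stability over levels with a method that returns one averaged effect. Outside drain use it states no contrast between levels, although two of its hypotheses and its pooling rule need one. That conclusion follows from the model and does not depend on the assumed risks.

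The odds-ratio drift is a caution, not a general failure. It is about 1-5% for factor odds ratios of 2-3 at risks of 10% or more, and small beside the confidence interval. It reaches about 10% only with a common outcome and a factor OR near 5, or with a still stronger factor. It would be wrong to conclude that stable effects will generally look unstable.

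The reach is the exploratory subgroup and observational analyses. The primary ANCOVA is unaffected.

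**What to change.** Replace the sentence in the addendum with the following.

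- For each factor, report the CryoSeal effect at each level and the difference between levels (the CryoSeal-by-factor interaction), each with 95% CI.
- Declare one scale per endpoint: the mean difference in degrees from the ANCOVA for extension, and one measure for yes/no endpoints, the same for crude and adjusted figures.
- Use this same contrast to judge homogeneity before the pooling in the observational analyses.
- Use correction for baseline factors for precision only, and do not interpret a change in an odds ratio after correction. Factors that arise after randomisation, such as transfusion or hospital stay, can move the estimate for other reasons and should not be used this way.

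The cost is wording and a little programming, with no new data. The downside is wide intervals. With about 36% power for a 10-degree difference between two equal-sized levels (SD 35, N = 500), an unremarkable interaction is not evidence of homogeneity, and the results should stay labelled exploratory.

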1. Hospital stay in days
2. Years of age

Categorized variables

1. Hospital stay: <3; 3-5; 6-8; >8 days
2. Age: >70; 70-60; <60 years of age

The subgroup analyses above are explorative for hypotheses screening.

Extra secondary analyses: Observational analyses of the RCT dataset:

When no correlation between the use of CryoSeal and the pre-, peri- and postoperative variables can be demonstrated and the above estimates are homogenous over the study arms, they will be pooled over the strata before further subgroup analysis; univariate followed by subsequent multivariate analysis will be performed.

The following research questions will be investigated by post-hoc analyses:

Preoperative variables:

1. Is there a correlation between preoperative hand grip strength and postoperative complications after > 1 year?
2. Are there associations between pre-op outcomes of the questionnaires and post-op functional/QoL/complications?
3. Is there a correlation between Range of Motion (ROM) and Oxford Knee Score outcomes?
4. Is there a correlation between preoperative NSAID (incl. Asperin) use and primary and secondary outcomes?
5. Is there a correlation between preoperative Prednison use and primary and secondary outcomes?

Perioperative variables:

1. Is there difference in post-op outcomes between LPS cemented vs cementless (Haga vs Spaarne) knee protheses
2. Is there difference in post-op outcomes (incl. hospital stay, body temp. (if applicable)) or -complications (incl. transfusion reactions) in transfused and non-transfused patients, or patients transfused at different indications/-triggers, and using different type of transfusion products
3. Are there more transfusion reactions in women?
4. Is there a difference in primary and secondary outcome between surgery type (“onder bloedleegte” or not)
5. Is there a difference in mean hospital stay and EPO use (if applicable)
6. Is there a correlation between wound catheter (incl. autologous reinfusion, if applicable) use vs no use and postoperative complications (bleeding, body temp).
7. Is there a correlation between perioperative wound drain reinfusion vs no reinfusion (if applicable) and postoperative complications
8. Is there a correlation between surgery time and postoperative outcomes of the questionnaires
9. Blood losses associated with type of catheter used
10. Is there a correlation between perioperative transfusion trigger (anaemia), age and length of hospital stay

Postoperative variables:

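### The age hypothesis concerns patients over 60, but its first-listed split is at 70 and the alternative grouping is left open

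*Combined protocol and SAP*

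**What the plan says.** The addendum (Analysis plan, Subgroup analyses) introduces three variables with "The following hypotheses will be tested using three for the variables stratified subgroups". The third is "Age > 70 and ≤ 70 years, or categorized in 3 equal sized samples of age", followed by a bracketed example with bands below 60, 60 to 70 and above 70. The hypothesis paired with it links age to co-morbidity and poorer wound healing, "which increase postoperative knee ROM and mobility effect of CS in patients > 60 years".

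On multiplicity the addendum states "There will be no correction for multiple testing because all subgroups are defined by variables" known to be related to the primary endpoints. It adds "All subgroups were specified before the data are available".

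The same age item, including its *or*, recurs among the combined subgroups of the 19-variable step. That step also lists years of age as a continuous variable and fixed categories, "Age: >70; 70-60; <60 years of age". A split into over 60 and 60 or younger appears only for transfused patients with a given transfusion trigger. The lists close with "The subgroup analyses above are explorative for hypotheses screening".

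**The concern.** The hypothesis and its first-listed analysis use different thresholds. With a cut at 70, patients aged 61 to 70 count as the reference group although the hypothesis places them among those who gain more. No option listed for this hypothesis is a direct comparison of >60 with ≤60.

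The *or* also leaves the coding unfixed, which sits badly with the statement that all subgroups were specified beforehand. The example bands agree with equal-sized groups only if the sample tertiles happen to fall at 60 and 70. The two texts also treat age exactly 60 differently: the hypothesis leaves it out of the older group, while the example puts it in the middle band.

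At stake is whether one of only three hypotheses singled out for testing is examined by an analysis that can show it, and whether a result can fairly be called pre-specified.

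**Working it through.** **Inputs from the documents.** Difference 10 degrees, SD 35 degrees, 250 per arm, 90% power (protocol section 4.4); two-sided level 0.049 (section 8). The documents give no age distribution and no power for the age subgroup.

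**The plan's own figure.** Power of the main comparison: 10 / (35·√(2/250)) = 3.194; 3.194 − 1.969 = 1.225; power 89.0%, close to the stated 90%. The same inputs give 259 per arm for exactly 90%. Nothing below depends on that small gap.

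**Dilution by the 70 split.** Assume a step: extra effect d above 60, none at or below 60.
- A cut at 60 tests d.
- A cut at 70 tests d × P(age ≤60) / P(age ≤70), because the reference group already contains the 60–70 patients.
- SE of the interaction contrast = 35·√(4/N₁ + 4/N₂), with N₁ + N₂ = 500, tested two-sided at 0.05.

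For equal thirds at 60 and 70 and d = 10, the SE is 35·√(4/166.7 + 4/333.3) = 6.6. The cut at 60 tests 10 degrees and the cut at 70 tests 5 degrees.

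| Assumed shares ≤60 / 60–70 / >70 | Contrast kept by 70 split | Power, cut at 60 (d = 10) | Power, cut at 70 (d = 10) |
|---|---|---|---|
| 33 / 33 / 33% | 50% | 32.5% | 11.7% |
| 25 / 40 / 35% | 38% | 28.2% | 9.0% |
| 20 / 40 / 40% | 33% | 24.8% | 8.2% |
| 15 / 35 / 50% | 30% | 20.7% | 7.7% |
| 10 / 35 / 55% | 22% | 16.0% | 6.4% |
| 10 / 50 / 40% | 17% | 16.0% | 5.8% |

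With age taken as normal, SD 9, the same ratio is 41%, 32% and 27% at mean age 65, 68 and 70.

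**The three-group option.** With bands at exactly 60 and 70, the under-60s stand alone and the contrast is intact. The 2-df test only costs some power: 25% against 32.5% at d = 10, and 77% against 85% at d = 20 (equal thirds). The 70 split has 32.5% at d = 20. True sample thirds dilute only if the lower tertile is away from 60. For example, if 15% are ≤60, the lowest third is 0.15/0.333 = 45% aged ≤60 and keeps 45% of the contrast.

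**The open choice.** In simulated null trials of 500 patients, taking the smaller p-value of the 70 split and the three-group interaction test rejects in about 7.5% when the thirds fall at 60 and 70. Simulations that drew ages from the normal distributions gave about 7.8–8.5%. The nominal rate is 5%.

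**The case against.** The strongest reply has five parts.

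- **The bracketed example contains a boundary at 60.** A reader might infer that no listed analysis can test the hypothesis. That goes too far: bands at 60 and 70 isolate the under-60s. Nor can the documents show that those bands are not thirds, because they give no age distribution.
- **The timing of the choice is not stated.** A reader might infer that the cut will be picked after the results are seen. The documents do not say so. The plan is to be registered before it is run on the closed database, tertiles depend on age and not on outcome, and subgroup results are to be discussed alongside all the others. What stands is that the *or* is unresolved, so such a choice is not ruled out.
- **The error rates belong to a test the addendum does not specify.** It describes subgroup odds ratios with confidence intervals; the only interaction term described is for drain use (protocol section 8). The 7.5–8.5% is therefore a worst case for an interaction test, not the error rate of the written analysis.
- **The dilution depends on a step at 60.** If the effect rose linearly with age (mean 68, SD 9), the 70 split would correlate 0.79 with age and a 60 split 0.69, so 70 would be the better cut. This stands as a limit on the size, but the hypothesis as worded names 60.
- **The consequence is limited.** The primary analysis is untouched and the subgroup work is called explorative. This stands, although the addendum sets these three hypotheses apart from the 19-variable screening, so readers will give them more weight.

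**Conclusion.** The mismatch is an internal contradiction in the addendum: a hypothesis at 60, a first-listed split at 70, and an alternative with no rule for choosing it. Under a step at 60, the 70 split keeps about half of the contrast if the thirds fall at 60 and 70, and about 17–41% under the other age mixes tried. Dilution is established for the 70 split only. The age shares and the shape of the effect are assumptions. The inflation to about 7.5–8.5% applies only if the better of two interaction tests is reported. This is a secondary matter, but worth correcting because the plan relies on pre-specification to justify making no multiplicity correction.

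**What to change.** Before unblinding, name one age analysis for this hypothesis: the arm-by-age interaction for >60 versus ≤60, added to the analysis of covariance of the continuous extension outcome. State which group age exactly 60 belongs to, and use that rule throughout. Delete the *or*. Label the 70 split, the 60/70 bands and continuous age as sensitivity analyses. A linear age term should not be the named test, because it does not test a threshold at 60 either.

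The cost is a wording change. The downside is that the ≤60 group may be small and its estimate imprecise. Power for a 10-degree interaction stays low, 16% to 32.5% over the age shares tabulated, so a null result should not be read as evidence that age does not matter.

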## 6.2 Randomisation, blinding and treatment allocation

Patients are included after signing the Informed Consent form. Patients will be stratified per clinic. Randomisation is done by web based computer application. Each centre will have its own username and password with a specific randomisation in blocks with a variable amount of patients. Block randomisation is used to get an equal distribution of patients in each treatment group for the interim and final analysis. Per randomisation patients characteristics like gender and date of birth are asked to prevent scrambling.

Each centre should randomise at least 50 patients to receive an equal distribution over the participating centres. Patient and assessors are blinded for the intervention by the patient. After 3 months follow-up, the treatment arm is communicated with the patient.

All patients are followed according to the intention-to-treat principle. Patients will be registered using a patient number, date of birth and study number and all other data will be coded by linkage to the study number.

An analysis plan will be enclosed as an addendum of this protocol 4.1 and before the study will be de-blinded.

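### The observational analyses may be pooled once no correlation with CryoSeal is shown, but that check has no criterion, has limited power and cannot detect confounding by clinic

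*Combined protocol and SAP*

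**What the plan says.** The rule is in the analysis plan addendum, under the extra secondary (observational) analyses. It has two conditions: "When no correlation between the use of CryoSeal and the pre-, peri- and postoperative variables can be demonstrated", and that "the above estimates are homogenous over the study arms". If both are met, "they will be pooled over the strata before further subgroup analysis", after which "univariate followed by subsequent multivariate analysis will be performed". The addendum gives no test, significance level or margin for either condition. It does not say which strata are meant, which covariates enter the multivariate models, or what happens if a condition fails.

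The list that follows is introduced by "The following research questions will be investigated by post-hoc analyses". It holds 18 items: 5 preoperative, 10 perioperative and 3 postoperative.

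Four other places bear on the point:
- Section 6.2: "Patients will be stratified per clinic", with randomisation in blocks of varying size within each centre. Section 3 gives six strata and notes that sites differ on postoperative wound drains.
- Addendum, perioperative questions: "Is there difference in post-op outcomes between LPS cemented vs cementless (Haga vs Spaarne) knee protheses".
- Addendum, postoperative questions: one type of drain (Bellovac) is used at a single hospital, with n=73.
- Addendum, statistical analyses: "When a preoperative variable is significantly associated with CrySeal use we will address this observation". Association with arm is there judged by significance.

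**The concern.** Not being able to show a correlation is different from showing that there is none. Without a margin, the rule is easiest to satisfy where the data are least informative.

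The second difficulty is what the rule looks at. Both conditions concern the treatment arm. For questions about drains, implants, transfusion or surgery time, the more plausible confounder is the clinic, because the plan itself ties some of these factors to particular hospitals. Arm is balanced within clinic by design, so clinics could differ widely in both factor and outcome while showing no correlation with CryoSeal use. A pooled univariate estimate could then present a difference between hospitals as an effect of a drain or an implant.

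**Working it through.** **Inputs from the documents.** 250 per arm, 10-degree difference, SD 35, level 0.049, 90% power (section 4.4); two-sided testing (section 8); total size limited to 400 to 600 (sections 4.4 and 8); six strata (section 3); 73 patients with the single-hospital drain (addendum).

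**Assumptions.** The pooling rule states no figures. I assume a two-sided 5% test, 1:1 allocation and the normal approximation. The effect sizes in steps 1 to 4 are illustrative unless marked as the plan's.

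**Planned size.** n per arm = 2(1.969 + 1.282)²(35/10)² = 259. At 250 per arm, power = Φ(10/(35√(2/250)) − 1.969) = Φ(3.194 − 1.969) = 0.890, about one point below the stated 90%. I use 250 as the planning size; nothing below depends on the difference.

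**Step 1: power to show a correlation with arm.** For a standardised difference d, power = Φ(d√(n/2) − 1.96).
- d = 0.2, n = 250: Φ(2.236 − 1.96) = 0.609, so it is missed 39% of the time. With 200 or 300 per arm, power is 0.516 or 0.688.
- d = 0.1, n = 250: power 0.200 (0.169 to 0.231 over the same range).
- Smallest d detected with 80% power: (1.960 + 0.842)√(2/250) = 0.25.
- A factor present in 20% of one arm and 27% of the other: power 0.454, so it is missed 55% of the time.

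**Step 2: power of the homogeneity condition.** A difference between arms in the effect of a factor equals the difference in arm effect between the factor's levels. Its standard error in SD units is √(4/n₁ + 4/n₂).
- 73 against 427 (total 500): √(4/73 + 4/427) = 0.253. A difference of 0.3 SD has power Φ(0.3/0.253 − 1.96) = 0.22.
- 250 against 250: standard error 0.179, power 0.39.

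**Step 3: clinic bias that the check cannot see.** Take two clinics of equal size, with factor prevalence q₁ and q₀ and mean outcomes 5 degrees apart. Bias in the pooled unadjusted factor estimate = 5 × [q₁/(q₁+q₀) − (1−q₁)/(2−q₁−q₀)].
- 60% and 40%: 5 × (0.6 − 0.4) = 1 degree.
- 80% and 20%: 5 × (0.8 − 0.2) = 3 degrees.
- Factor fixed by clinic: 5 × (1 − 0) = 5 degrees, the whole clinic difference.

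With arm balanced within each clinic, none of this produces a correlation between factor and arm.

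**Step 4: bias from leaving out arm.** With prevalence 27% and 20% by arm and the plan's 10-degree effect: 10 × (0.27/0.47 − 0.73/1.53) = 10 × 0.097 = about 1 degree. Randomisation makes such an imbalance unlikely in a preoperative factor. It is more plausible in a peri- or postoperative variable, which treatment can change.

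**The case against.** The strongest reply has four parts.

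*The text does not say that arm and clinic are discarded.* A reader might infer that data are merged across arms and clinics. The sentence says only that something is pooled over strata, and elsewhere in the addendum stratification refers to catheter, NSAID and age subgroups. Checking stratum estimates for homogeneity and then combining them is ordinary Mantel-Haenszel-type practice, which keeps the stratification. This stands: the text is ambiguous, and the stronger reading is not supported.

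*Multivariate analysis follows.* A reader might conclude that arm and clinic effects remain in the final estimates. The documents do not establish that, since the later models could include both terms. But no model in the plan names clinic: the section 8 analysis of covariance adjusts for preoperative angle, with drain use added in a secondary model, and clinic is not among the addendum's subgroup variables. The univariate step is unadjusted as written.

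*The harm from the arm pre-test is small.* Arm confounds only if it is related to both factor and outcome. At the plan's own effect (10/35 = 0.286 SD), a 5% test has 89% power. Missing both that and a 0.2 SD factor association has probability of about 0.39 × 0.11 = 4%, assuming independence. The bias in a standardised slope would then be 0.0995 × 0.141 = 0.014, against a standard error of about 1/√500 = 0.045, and 95% coverage would fall to about 94%. This also stands. It disposes of any suggestion that intervals after the pre-test are seriously too narrow.

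*Clinic confounding is a separate matter from the rule.* The rule neither causes nor cures it, and the plan itself names the hospitals for the two clearest contrasts. That is correct, but it supports the point: the only safeguard stated before pooling does not address the main threat.

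It would also go too far to say that surgical technique differs by clinic. The tourniquet and application techniques are not tied to sites in the documents.

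**Conclusion.** The point holds as a minor one. The plan lets absence of evidence license pooling, under two conditions that lack criteria and have limited power at the planned size. Those conditions cannot reveal confounding by clinic. The univariate pooled estimates are exposed to clinic differences, and removal of arm and clinic effects in the multivariate step is not ensured.

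The power figures rest on the assumed 5% two-sided test. The clinic bias of 1 to 5 degrees rests on an assumed 5-degree difference between clinics and shows the mechanism only. That cement type is fixed by clinic is inferred from two hospitals being named in one question; the single-hospital drain is stated outright. Confounding of preoperative factors by arm should be small. The primary analysis and the randomised comparison of CryoSeal are not touched.

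**What to change.** In the addendum:
- Delete the pooling condition. Fit each observational model on all patients, with arm and clinic (the randomisation stratum) as fixed terms, and list the other covariates.
- Where effect modification by CryoSeal is of interest, report the arm-by-factor interaction with its confidence interval in place of a judgement of homogeneity.
- Where clinic determines the factor (cement type at Haga versus Spaarne, Bellovac at one hospital), omit the clinic term, because the contrast cannot be separated from clinic. Report it as a clinic comparison, not as an implant or drain effect.

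The cost is a change of wording and, with six strata, 5 + 1 = 6 degrees of freedom in about 500 patients. Factors that vary mostly between clinics will be estimated less precisely. No new data and no change in sample size are needed.
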